#### Exploratory analyses

Any lateralisation that occurs in MCI/AD is likely to be limited, therefore, any impairment in peripheral reaching may be similarly non-lateralised. An average PMI (across both sides) will therefore be calculated to assess peripheral reaching ability overall. More detailed analyses will be run with a between-subject factor of group and within-subject factors of side, eccentricity and viewing condition. These analyses will be conducted using dependent variables of absolute reaching error, directional (signed) reaching error, reaction time and movement time. The expectation is that peripheral misreaching will manifest as a fixation-directed bias, which is exacerbated at higher eccentricities significantly more so in patient groups than in age-matched controls.

### Radial reaching task

IRED speed is used to determine onset and offset of the reaching movement. Movement onset is defined as the first frame in which the IRED’s speed exceeds 50 mm/s (and maintains that speed for up to 100 ms). Movement offset is defined as the first subsequent frame in which IRED speed falls below 50 mm/s. The landing position of the movement is defined by the x-coordinate and y-coordinate in the final frame of the movement and will be recorded as errors relative to true target locations recorded during calibration for each participant.

An initial analysis of PMI for the radial reaching task will be performed, restricted to the two most eccentric target positions (33.4° and 43.6°). Case–control comparisons follow the plan for the lateral reaching task (Analysis of single case deficits section), to estimate the rates of peripheral misreaching, and borderline peripheral misreaching, in the two patient groups. Due to different experimental set-ups between the two test sites (UoE, UEA), each patient will be referenced to the same-site control data for case–control comparisons.

A group level ANOVA of PMI, restricted to the two most eccentric target positions, will similarly follow the plan for lateral reaching (Group-level analysis section). We will include site (UoE, UEA) as an additional covariate. More detailed analyses will also follow the plan for lateral reaching. Since motion tracking also provides kinematic variables on reaching trajectories, we also aim to examine the dependent variables peak speed and time to peak speed, normalised time after peak speed until reach endpoint and number of secondary movements.

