#### ​Radial reaching tasks

##### Stimulus and Apparatus

An infrared motion-tracking camera (Optotrak Certus, Northern Digital) is used to track the reaching movement. Infrared-emitting diodes (IREDs) are taped to the tip of the right and left index fingers of each participant to track the reach in each hand. The Optotrak samples the IRED’s 3D position at 100 Hz throughout each 2000 ms trial. The task is controlled by custom software written in LabView (National Instruments) programming environment. The stimuli and apparatus reported here are specific to UoE. At the second site, UEA, motion tracking was performed by using a Qualisys system (Gothenburg, Sweden) and a slightly different set up was used. 14

Participants are seated with their head placed in a chin-rest in line with the middle of the display. Stimuli are back-projected via a mirror onto a screen (1000 mm wide × 750 mm deep) that lies flat in-front of the participant. A webcam is placed on the screen 50 cm directly in-front of the participant, as a fixation point. The live webcam image feeds into a separate laptop, allowing the experimenter to monitor gaze. A start button is aligned to the centre of the screen, positioned 10 cm in-front of the participant, 40 cm away from fixation (figure 2). Targets are white circles (diameter=1.60°, 13.96 mm) presented at four eccentric locations (11.4°, 22.6°, 33.4° and 43.6° away from centre) on each side (figure 2).

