##### Free reaching

Participants initiate a trial by pressing and holding down the start button. As soon as they push the button down, participants may look around the screen for a target. After 250–750 ms a target appears, participants then look directly at the target and reach to touch the target in one smooth movement. Optotrak recording is initiated simultaneously with target appearance, and the target disappearance is simultaneous with the end of the recording after 2000 ms. When the target disappears a short beep (100 ms, 440 Hz) plays, the participant leaves their finger at its landing position until they hear the beep. After the trial, the experimenter codes the trial validity with a key-press; ‘Return’—valid, ‘F1’—no eye-movement, ‘Esc’—void trial. If an invalid trial (‘F1’ or ‘Esc’) is coded the trial gets recycled to the end of the block.

The block ends once 28 valid trials (7 per target location) are recorded, or after 50 valid and ‘no eye-movement’ trials.

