##### ​Peripheral reaching

To assess reaching accuracy in the periphery participants are required to look directly at central fixation (the webcam) throughout each trial. Participants initiate a trial by pressing and holding down the start button. After 250–750 ms a target appears. While maintaining gaze on the webcam participants make one smooth reaching movement to try to touch the target. After the reach, participants leave their finger at its landing position until a short beep (100 ms, 440 Hz). The target remains on screen for 2000 ms after the trial begins. The motion-tracker records the reach throughout the 2000 ms trial. At the end of the trial, the experimenter codes trial validity; ‘Return’—valid trial, ‘F1’—eye movement during trial, ‘Esc’—void trial. If an invalid trial (‘F1, ‘Esc’) is recorded then the trial is recycled to the end of the block.

The block ends after 28 valid trials (7 per target location) are recorded, or after 50 valid and ‘eye-movement’ trials.

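### The radial-task onset rule gives the 100 ms duration as a maximum rather than a minimum, so a single frame above 50 mm/s can start a movement

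*Protocol article*

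**What the plan says.** All places are in the protocol article.

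- **Onset** (Analysis plan, Radial reaching task): the first frame in which finger "speed exceeds 50 mm/s (and maintains that speed for up to 100 ms".
- **Offset** (same section): "Movement offset is defined as the first subsequent frame in which IRED speed falls below 50 mm/s". No time below threshold is required.
- **Scored endpoint** (same section): the x and y coordinates "in the final frame of the movement and will be recorded as errors relative to true target locations recorded during calibration".
- **Later movements** (same section): listed among further kinematic variables, as "normalised time after peak speed until reach endpoint and number of secondary movements". The text does not say whether a secondary movement changes the scored endpoint.
- **Sampling** (Radial reaching tasks, Stimulus and Apparatus): the marker's "3D position at 100 Hz throughout each 2000 ms trial". This describes the Edinburgh set-up; the East Anglia site uses a different tracker whose rate is not given.
- **Timing, free reaching**: "Optotrak recording is initiated simultaneously with target appearance, and the target disappearance is simultaneous with the end of the recording after 2000 ms".
- **Timing, peripheral reaching**: the participant starts a trial by pressing the button, the target follows after 250–750 ms, and then "The target remains on screen for 2000 ms after the trial begins".

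**The concern.** The duration condition in an onset rule exists to reject short bursts of speed that are not the reach. A maximum cannot do that: any run above threshold qualifies, down to one frame. Offset is the next frame below threshold, so a false onset also fixes a false landing position, close to the start button and far from the target.

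Radial endpoint error feeds the radial PMI, and from it the planned rates of misreaching and borderline misreaching in both patient groups and the group-level ANOVA. An analyst who codes the rule as printed and one who silently reads it as a minimum would get different endpoints from the same recordings whenever a twitch precedes the reach.

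Two neighbouring statements leave related room for doubt. Secondary movements are counted, and participants keep the finger where it landed until the beep, so a final resting position is recorded as well as a first stop. The two viewing conditions also describe the start of their 2000 ms differently, although the PMI subtracts one from the other.

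**Working it through.** The protocol states no figure here to reproduce. The check applies the printed rule to constructed reaches.

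**Inputs from the protocol:** threshold 50 mm/s; sampling 100 Hz, so one frame is 10 ms, 100 ms is 10 frames and a 2000 ms recording is 200 frames; foreperiod 250–750 ms.

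**Assumptions (not in the protocol):** minimum-jerk movements, x(s) = A(10s³ − 15s⁴ + 6s⁵) with s = (t − t₀)/T; total distance 400 mm; all amplitudes, durations and pauses below. In the twitch cases the twitch starts at 300 ms and the main reach at 600 ms, lasting 700 ms.

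**Step 1, onset.** Scored landing position on a 400 mm path:

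| Reach | Frames of twitch above 50 mm/s | As written (1 frame) | Minimum 10 frames |
|---|---|---|---|
| Single smooth reach, 700 ms | none | 399.7 mm | 399.7 mm |
| 5 mm twitch over 100 ms, then reach | 5 | 4.7 mm | 399.3 mm |
| 5 mm twitch over 120 ms, then reach | 5 | 4.5 mm | 399.3 mm |
| 10 mm twitch over 120 ms, then reach | 7 | 9.6 mm | 399.3 mm |
| 10 mm twitch over 150 ms, then reach | 10 | 9.8 mm | 9.8 mm |

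For the 5 mm, 100 ms twitch the shortfall falls from 400 − 4.7 = 395.3 mm to 400 − 399.3 = 0.7 mm. The last row shows the limit of the correction: a twitch that itself stays above threshold for 10 frames still passes.

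**Step 2, offset.** A two-step reach of 300 + 100 mm with a 50 ms gap is scored at 299.7 mm (100.3 mm short), and one of 370 + 30 mm at 369.6 mm (30.4 mm short). Both results are the same with a 1-frame or a 10-frame onset. Requiring speed to stay below threshold for 10 frames at offset also leaves them unchanged, because the slow tails on each side of the gap lengthen the time below 50 mm/s. The open question is therefore which endpoint is meant, and a 100 ms stop criterion would not settle it.

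**Step 3, window.** If the peripheral clock ran from the button press, the time left after target appearance would be 2000 − 250 = 1750 ms down to 2000 − 750 = 1250 ms, a loss of 12.5% to 37.5% against free reaching. If it runs from target appearance, the loss is zero.

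**Step 4, from one trial to the PMI.** There are 7 valid trials per target. If the lateral task's median per eccentricity carries over, 4 of 7 trials must be affected before the median is itself a faulty trial. With 3 of 7 affected, the median is the largest error among the 4 clean trials.

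**The case against.** The strongest reply is that the intent is plain: a condition that speed be maintained has no function if one frame satisfies it, so the wording is a drafting slip. That is probably right about intent, but the sentence is the scoring rule and should be executable as printed.

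A reader might infer that the rules as a whole cause hesitant or slow reaches to be classed as misreaching. The protocol does not support that, for these reasons:

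- Taking the first drop below threshold is a defensible endpoint for the primary movement. It fits the instruction to make one smooth reach and the separate count of secondary movements. The lateral task also ends at the first touch, wherever it lands.
- A slow but continuous reach is scored correctly while it stays above 50 mm/s.
- Twitches common to both viewing conditions are the kind of general motor factor the free-reaching baseline is meant to remove. Nothing in the protocol shows that they are more frequent in peripheral reaching.
- Void trials are repeated, medians absorb isolated faults if they are used, and each patient is compared with same-site controls.

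These protections are incomplete. The void code has no stated criterion for a twitch or a pause, and controls with extreme PMI values are excluded and replaced, which may narrow the reference range.

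A reader might also infer that peripheral reaching has a shorter response window. That is only one reading. The same sentence keeps the target visible for 2000 ms, the apparatus section gives one 2000 ms trial for the task, and in free reaching "Optotrak recording is initiated simultaneously with target appearance". These favour 2000 ms from target appearance in both conditions. What stands is that the two descriptions should agree.

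**Conclusion.** The onset rule is wrong as written: it gives a maximum duration where a minimum is needed. On the assumed trajectories, a short twitch moves the scored landing position by almost the whole reach (395.3 mm of 400 mm), while single smooth reaches are unaffected. The size per trial rests on assumed movement shapes; how often such twitches occur cannot be known from the protocol.

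Added error in radial endpoints follows if the rule is applied literally. Bias in the radial PMI is possible but not shown: it would need many affected trials at a target, more of them in peripheral than in free reaching, and more in patients than in the same-site controls. The endpoint definition and the time origin are points to clarify, not demonstrated errors. The sample size and main inferential analyses rest on the lateral task and are untouched.

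**What to change.** 1. Define onset as the first frame from which speed stays above 50 mm/s for at least 100 ms (10 frames at 100 Hz). State it in milliseconds so that it carries over to the second site's tracker.
2. Apply the same rule to the stored control data at both sites and to all patients, including the 8 of 48 already tested when the article was written.
3. State whether the scored endpoint is the end of the primary movement or the final resting position before the beep.
4. Reconcile the free and peripheral reaching descriptions so that the 2000 ms run from target appearance in both. If the recordings were made otherwise, say so.

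The cost is three sentences and a rerun of the scoring on stored trajectories. The corrected onset rule will still accept twitches that last about 100 ms or more above threshold, so it reduces false onsets without removing them all.

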### Power considerations

The target sample sizes (N=24 per group) are based on power considerations related to the main inferential analyses, the case–control comparisons and binomial tests of rates of peripheral misreaching deficits for the lateral reaching task.

The control sample size of 24 will provide close to the maximum power for case–control tests of deficit (figure 3A). Note that high power for these comparisons is inherently unachievable unless the deficit being tested for is very large. We do not know how large any misreaching deficits may be in our patient groups, but our control sample size will provide close to the maximum achievable power to detect them if they exist. Figure 3B illustrates more fully the relationship between deficit size (D) and power, for the adjusted alpha level (0.025) and unadjusted alpha level (0.05) by which we will determine peripheral misreaching deficits and borderline cases, respectively (Analysis of single case deficits section).

The main hypothesis is that peripheral misreaching will be found in a significant proportion of patients with AD and MCI. For one-sample binomial test to determine whether the observed rate of peripheral misreaching exceeds the chance level of 0.05, a sample size of 24 has >0.9 power. Provided that the true population proportion is at least 0.2 (1 in 5). This is appropriate to our aims, since peripheral misreaching would be of limited significance in these clinical populations if its prevalence were less than 1 in 5.

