### Participants

Patients with a diagnosis of amnestic MCI or typical (amnestic) mild-to-moderate AD will be invited to take part. To ensure mild-to-moderate cases of AD, patients will have a score >50 in the most recent administration of Addenbrooke’s Cognitive Examination (ACE-III).^11^ If there is no recorded ACE-III score, clinical opinion of patient’s condition will be used to assess eligibility.

Older adults without any known neurological disorders will be tested as an HC group. To achieve our target of 24 full datasets per group (Power considerations section), we plan to test up to 30 participants in each group, allowing for possible withdrawals.

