**Figure 3 F3:**
[figure not shown]
Relation between(A) control sample size and power to detect a single-case deficit in a one-tailed test, for different sizes of deficit (D, expressed as SD of control mean). (B) D and power to detect a deficit, given a control sample size of 24, for adjusted (.025) and unadjusted (.05) alpha criteria.

We will next assess, for each side, whether the PMI of controls is related to age or sex, by computing Pearson’s correlations. If the correlation is ≥0.3 on either side, then that variable will be included as a covariate in the subsequent case–control comparisons for both sides.

Case–control comparisons will then be run to compare each patient’s PMI against control performance on each side of space. These comparisons will be based on Crawford and Howell's^15^ modified t-test; or, if covariates are included, we will use the Bayesian Test of Deficit with covariates.^16^ The individual tests will be one-tailed, with an alpha level set to 0.025, in order to constrain per-patient alpha level (across the two sides) to 0.05. If a patient shows a deficit on either side that meets the adjusted criterion (0.025), they will be classified as showing periperheral misreaching. If a patient shows a deficit on either side that would meet the unadjusted criterion (0.05), but not the adjusted criterion, they will be classified as showing borderline peripheral misreaching.

Finally, a binomial test will test whether the rate of observed peripheral misreaching exceeds the rate expected by chance (ie, the per-patient adjusted alpha level of 0.05). A significant outcome (p<0.05) for either patient group will indicate that peripheral misreaching is a feature of this patient group. The observed rate of peripheral misreaching will provide an estimate of how common it is. We will run a further analysis including borderline cases and compare the rate of peripheral misreaching in each patient group against the appropriate chance level of 0.10.

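### The main binomial test has power 0.74, not above 0.9, at a true rate of 1 in 5 with 24 patients

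*Protocol article*

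**What the plan says.** The Power considerations section ties the group sizes to the main tests: "The target sample sizes (N=24 per group) are based on power considerations related to the main inferential analyses". For the main hypothesis it considers a one-sample binomial test of "whether the observed rate of peripheral misreaching exceeds the chance level of 0.05" and states that "a sample size of 24 has >0.9 power. Provided that the true population proportion is at least 0.2 (1 in 5"). It then calls this suitable for the study's aims, because a prevalence below 1 in 5 would matter little in these populations.

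The test is defined under Analysis of single-case deficits. Each patient is classified from two one-tailed tests, one per side, each at 0.025. Then "a binomial test will test whether the rate of observed peripheral misreaching exceeds the rate expected by chance", with chance set at the per-patient level of 0.05. The decision rule is applied to each patient group separately: "A significant outcome (p<0.05) for either patient group will indicate that peripheral misreaching is a feature of this patient group".

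Under Participants, 24 is the number of full datasets sought per group: "we plan to test up to 30 participants in each group, allowing for possible withdrawals".

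**The concern.** A binomial test with 24 patients and a null rate of 0.05 can only reject at whole counts, and the expected number of chance classifications is 24 × 0.05 = 1.2. At a true rate of 0.20 the expected count is 24 × 0.20 = 4.8. If the cut-off is 4, the expected count lies only just above it, and power above 0.9 is implausible on sight.

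The figure matters because it justifies the size of the two patient groups and because the section presents the design as adequate for the smallest rate of interest. A reader who trusts it may take a non-significant result in either group as good evidence against a 1-in-5 rate. With the correct power, such a result is much weaker evidence.

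**Working it through.** **Inputs, all from the protocol article**

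- n = 24 per patient group (Power considerations; Participants).
- Null rate p0 = 0.05 (Power considerations; Analysis of single-case deficits).
- Significance at p<0.05, judged per patient group (Analysis of single-case deficits).
- Direction: upper tail, since the question is whether the rate exceeds chance.
- Alternative p1 = 0.20, stated power above 0.9 (Power considerations).

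**Step 1: cut-off.** Find the smallest r with P(X ≥ r | 24, 0.05) ≤ 0.05, where P(X = k) = C(24, k) p^k (1−p)^(24−k).

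| k | P(X = k), p = 0.05 | P(X ≥ k), p = 0.05 |
|---|---|---|
| 0 | 0.2920 | 1.0000 |
| 1 | 0.3688 | 0.7080 |
| 2 | 0.2232 | 0.3392 |
| 3 | 0.0862 | 0.1159 |
| 4 | 0.0238 | 0.0298 |

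Three classified patients are not significant (0.116); four are (0.030). The cut-off is r = 4, with an exact size of 0.030. The exact two-sided test has the same upper cut-off (p = 0.030 at 4, 0.116 at 3), so sidedness does not change the result.

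**Step 2: power at 0.20.**
P(X ≤ 3 | 24, 0.20) = 0.0047 + 0.0283 + 0.0815 + 0.1493 = 0.2639 from unrounded terms.
Power = 1 − 0.2639 = **0.736**. The stated figure is not reproduced.

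**Step 3: other ways to run the test in one group of 24, at 0.20**

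| Version | Power |
|---|---|
| Exact, one-sided or two-sided 0.05 (r = 4) | 0.736 |
| Mid-p (r = 4) | 0.736 |
| Randomised to use the full 5% | 0.771 |
| Arcsine approximation | 0.754 |
| Normal approximation, continuity-corrected | 0.754 |
| Normal approximation, null and alternative variances | 0.827 |
| Cut-off of 3 (true size 0.116, not valid) | 0.885 |

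The uncorrected normal approximation is Φ[(0.15√24 − 1.645√(0.05 × 0.95)) / √(0.20 × 0.80)] = Φ[(0.7348 − 0.3585) / 0.4] = Φ(0.941) = 0.827. Power falls as the cut-off rises, and the cut-off of 3 already gives less than 0.9. A fixed cut-off would have to be 2 or lower to exceed 0.9, and the size at 2 is 0.339.

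**Step 4: what would give 0.90.**
- At n = 24, P(X ≥ 4) reaches 0.90 at a true proportion of about 0.258 (0.885 at 0.25, 0.905 at 0.26).
- At a true proportion of 0.20, the exact test first exceeds 0.90 at n = 38 (0.901) and stays above it from n = 45. Between these, power dips when the cut-off moves from 5 to 6.

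**Step 5: what a non-significant result would leave open.** Exact 95% confidence intervals are 0.027 to 0.324 for 3 of 24 and 0.010 to 0.270 for 2 of 24. Both include 0.20.

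**The case against.** The strongest defence is that some reading of the sentence gives a figure above 0.9. Four were tried.

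- **Success in at least one of the two patient groups.** If both have a true rate of 0.20 and are independent, this is 1 − (1 − 0.736)² = 0.930. Pooling the groups (n = 48, cut-off 6) gives 0.938. But the sentence gives the power for a sample of 24, and the decision rule draws its conclusion about each patient group by itself.
- **0.2 as true prevalence, with false positives added.** With perfect detection, the classified rate is 0.20 + 0.80 × 0.05 = 0.24 and power is 0.862, still short of 0.9. The protocol itself calls the single-case tests low powered. If sensitivity is assumed to be 70%, the classified rate is 0.18 and power is 0.65; at 50% they are 0.14 and 0.44. On this reading 0.74 may be generous.
- **Up to 30 tested.** The surplus covers withdrawals. If all 30 were analysed, the cut-off would be 5 and power 0.745.
- **A normal approximation using the null variance alone.** This gives Φ(0.15√(24/0.0475) − 1.645) = 0.958. It may be where the figure came from, but the article names no method, so that is conjecture. It ignores the larger variance at 0.20 and is not the power of the test.

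Three points limit the consequences, and they stand. The number of controls rests on the case–control power curves, which this error does not touch. The binomial test is accompanied by an analysis with borderline cases and a group-level ANOVA, so it is not the only way to see an impairment. And the article does not say that a null result excludes a rate of 0.20; that over-reading is a risk the figure invites. None of these corrects the figure.

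**Conclusion.** The concern holds. For each patient group of 24, the power of the stated test at a true proportion of 0.20 is 0.736, at least 16 percentage points below the claim. The miss rate is 26% instead of under 10%. The design reaches 0.90 only from a true proportion of about 0.26, roughly 1 in 4.

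The result uses only inputs in the article. It takes 0.20 as the proportion of patients whom the procedure classifies as misreaching, and takes the classifications as independent with a chance rate of exactly 0.05, as the plan does. The validity of the test is unaffected: its exact size is 0.030. The error concerns the justification of the patient group sizes and the weight that a non-significant result can bear. Because this is the only numerical power given for the main hypothesis, it must be corrected.

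**What to change.** In Power considerations, replace the power sentence with wording such as: 'With 24 patients in a group, the exact binomial test against 0.05 is significant at 4 or more classified patients (exact size 0.030). Power is 0.74 at a true proportion of 0.20 and reaches 0.90 at about 0.26.' State that 0.20 here means the classified proportion, and that imperfect detection lowers the power if it is meant as true prevalence.

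The 1-in-5 rate can stay as the smallest rate of interest. The statement that the design is adequate for it should go.

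In addition, specify that each group's observed rate is reported with an exact 95% confidence interval, so that a non-significant result is not read as excluding 0.20. This is a useful safeguard, separate from correcting the figure.

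The cost is wording only: no extra patients, and no change to the test, its cut-off or the data collected. The stated power becomes less favourable. The article reports 8 of 48 patients tested, so at that stage the correction could be made well before results.
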